When applied at a frequency that corresponds to the frequency range of endogenous neural oscillations (0.1–80 Hz) and in the so-called “ripple range” (140 Hz) (Moliadze et al., 2010), tACS may be able to interact with ongoing rhythms in the cortex by synchronizing them with the applied tACS current sine wave, which itself acts as an exogenous oscillation. When applied in the low kHz range (1–5 kHz), tACS is able to selectively target the membrane excitability of neurons by altering the accumulation of calcium in the presynaptic nerve terminals (Citri and Malenka, 2008), but this kHz range does not entrain with or synchronize neuronal oscillatory activity due to the low-pass filtering properties of the neuronal cell membrane (Antal and Paulus, 2013). On the other hand, tTIS involves the simultaneous application of two or more independent sinusoidally oscillating current waveforms at slightly different high frequencies, which alone do not influence neuronal activity due to the neuronal membrane’s low-pass filter (Grossman et al., 2017, 2018; Lozano, 2017). The combination of two high-frequency sine waves of slightly different frequencies (e.g., 1,000 and 1,130 Hz), however, generates two electric fields that overlap and form a high-frequency carrier wave (the average of the two input frequencies, 1,065 Hz) that is modulated by a low-frequency envelope oscillating at the much lower “beat” frequency that represents the absolute difference of the two sinusoids (e.g., 130 Hz). tTIS effects depend on this “beat” interaction to drive neuromodulation. Since the strength of the stimulation at any given location is determined by the electric field that is lower in amplitude, the resulting focus is much smaller and enables better targeting. Mechanistically and much like for conventional tACS, it has been shown that tTIS alters the timing, but not the rate, of neuronal spiking activity, with the exception that tTIS offers a way to disrupt pathological oscillatory activity focally and reduce neural synchrony in deep brain structures (Vieira et al., 2024).

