The basis of a more specific role of the sgACC in MDD is grounded in abundant afferent and efferent connections between the sgACC and the insula, brainstem, and hypothalamus, evident in autonomic and circadian components of emotion regulation, including stress response, as well as alterations in sexual functioning, sleep, appetite, neuroendocrine, and neuroimmune functioning (Freedman et al., 2000; Vertes, 2004; Ghashghaei et al., 2007; Hsu and Price, 2007). Reciprocal pathways linking the sgACC BA25 to orbitofrontal, medial frontal, and dorsal prefrontal cortices, the anterior and posterior cingulate cortices, and the amygdala, hippocampus, and nucleus accumbens further identify plausible pathways through which interceptive and homeostatic processes might influence aspects of learning, memory, reward, and reinforcement (Haber et al., 2006; Petrides and Pandya, 2007), which are the core cognitive and behavioral components impaired in depressed individuals. These structural and functional connections display considerable overlap with patterns of regional changes observed in response to pharmacotherapy and CBT, providing a solid foundation to pursue strategies that might effectively alter the sgACC connectivity in individuals with MDD rather than focusing on merely normalizing the absolute activity of the sgACC in isolation. The repeated observations of cellular abnormalities in the sgACC of depressed patients post-mortem, studies of acute emotional states, and predictable decrease in the sgACC activity in response to pharmacological and somatic antidepressant treatments provide a solid foundation to test the therapeutic potential of direct modulation of the sgACC (BA25) using high-frequency tTIS as a novel intervention strategy.

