Our primary aim is to demonstrate target engagement of the sgACC with tTIS in participants with MDD using the resting-state fMRI, arterial spin labeling (ASL), and diffusion-weighted MRI, as evidenced by pre- vs. post-treatment changes in its intrinsic activity, functional connectivity (FC), perfusion, and anatomical connectivity with other brain regions. We hypothesize that in participants with MDD, a course of 10-day active 130 Hz tTIS will induce engagement of the sgACC post-treatment, which will be superior to sham. Target engagement will be measured as pre- vs. post-treatment change in: (a) resting-state blood-oxygen-level-dependant (BOLD) activity, quantified by power in the BOLD characteristic frequency range (0.015–0.08 Hz), (b) perfusion metrics of cerebral blood flow (CBF), and (c) BOLD activity and CBF in resting-state functional and anatomical networks, or brain regions that are strongly coherent with the sgACC functionally and connected anatomically. We hypothesize that we will observe (a) an increase in BOLD activity in sgACC voxels in tTIS arms but not the sham due to the direct stimulation of the area, (b) an increase in CBF in sgACC voxels in tTIS arm but not the sham due to the direction stimulation of the area, (c) an increase in FC between sgACC and dorsolateral prefrontal cortex (dlPFC), ventromedial prefrontal cortex (vmPFC), and insula – the nodes that display reduced baseline resting-state FC in unmedicated MDD patients compared to healthy controls (Murrough et al., 2016; Wang et al., 2018; Cheng et al., 2021), (d) a significant association between changes in the FC of the sgACC with the abovementioned nodes and anatomical connectivity. Our secondary aim is to demonstrate, using a randomized sham-controlled design, the feasibility, tolerability, and therapeutic potential of repetitive tTIS in participants with MDD. We hypothesize that a 10-day active 130 Hz tTIS will produce significantly greater improvement than sham stimulation in scores of standardized clinical measures of mood symptoms severity in MDD, anxiety, quality of life, and functional impairment. We will also perform exploratory analyses of (a) pre- vs. post-stimulation changes in whole-brain resting-state FC of the sgACC, (b) pre- vs. post-stimulation changes in resting-state electroencephalography (EEG) spectral power after a single session of tTIS and over the course of 10 sessions, (c) pre- vs. post-stimulation changes in the amplitude and latency of the auditory mismatch negativity (MMN) event-related potentials (N1 and P1) after a single session of tTIS and over the course of 10 sessions, (d) feasibility of performing concurrent EEG acquisition during tTIS (termed tTIS-EEG), and (e) source signal propagation during concurrent tTIS-EEG using our proposed configuration for the stimulation of the sgACC with tTIS.

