### 3.12 Analysis plan

#### 3.12.1 Primary outcomes: target engagement

BOLD activation (power in the 0.015–0.08 Hz frequency range), CBF, seed-based resting-state FC, and anatomical connectivity of the sgACC will be the primary outcome measures to demonstrate sgACC target engagement with a course of tTIS. We hypothesize that we will observe an increase in the BOLD activation and CBF in the sgACC voxels in the tTIS arm but not the sham and an increase in resting-state FC between the sgACC and bilateral dlPFC, vmPFC, and insula in the tTIS arm but not the sham. We also hypothesize that changes in the resting-state FC will be associated with changes in anatomical connectivity between the sgACC and the abovementioned brain regions. Additional exploratory analyses of changes in the whole-brain FC of the sgACC and their association with anatomical connectivity will be performed.

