T1-weighted and T2*-weighted images will be preprocessed, with steps including volumetric segmentation and surface extraction, normalization, motion correction, field unwarping, bias field correction, and brain extraction (Esteban et al., 2019). Preprocessing and denoising will be performed using tedana: TE Dependent ANAlysis v.23.0.1 pipeline^1^ (Kundu et al., 2012, 2013; DuPre et al., 2021), which includes slice timing correction, estimation of motion correction, spatial normalization, signal distortion correction, smoothing, and filtering. The left and right sgACC will be identified using the Desikan-Killiany (FreeSurfer) anatomical labeling scheme (Desikan et al., 2006). Pre- vs. post-treatment changes in sgACC time series properties, such as BOLD activity, will be assessed using Wilcoxon signed-rank tests or paired *t*-tests on signal variance at each sgACC voxel. pCASL scans will be used for perfusion detection using the BASIL toolset to conduct simple CBF quantification in the sgACC voxels (Chappell et al., 2009). In addition, seed-based resting-state sgACC FC maps will be computed by calculating Pearson correlation coefficients between the BOLD time series across the rest of the brain, with a focus on bilateral dlPFC, vmPFC, and insula, and the sgACC voxel-averaged seed time series. Using SPM12, 5 mm spherical seeds will be created around the sgACC MNI coordinates, and contrast analysis on the FC will be run using CONN Toolbox v.22a (RRID:SCR_009550, v.22a) (Nieto-Castanon and Whitfield-Gabrieli, 2021). FC-based target engagement will be defined as statistically significant pre- vs. post-treatment changes in these sgACC FC maps, as computed with mass univariate paired *t*-tests.

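### The written rule for FC-based target engagement counts a significant change in either direction, although the primary hypothesis is an increase at named regions that exceeds sham

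*Protocol article*

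**What the plan says.** Section 3.12.1 makes seed-based functional connectivity (FC) of the sgACC one of the primary outcome measures and fixes how it will be judged: "FC-based target engagement will be defined as statistically significant pre- vs. post-treatment changes in these sgACC FC maps", "as computed with mass univariate paired" t-tests. The maps correlate the sgACC seed with the rest of the brain, with a stated focus on dlPFC, vmPFC and insula.

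The hypothesis in the same section is narrower: "an increase in resting-state FC between the sgACC and bilateral dlPFC, vmPFC, and insula in the tTIS arm but not the sham". Section 2 predicts the same increase, justifies the choice of regions as "the nodes that display reduced baseline resting-state FC in unmedicated MDD patients compared to healthy controls", and requires engagement in the active arm to be superior to sham. Both sections class changes in whole-brain FC of the sgACC as exploratory.

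For activity, Section 2 predicts "an increase in BOLD activity in sgACC voxels in tTIS arms but not the sham", and likewise for cerebral blood flow (CBF). Section 1.3 describes sgACC hyperactivity in more treatment-resistant patients and a "predictable decrease in the sgACC activity in response to pharmacological and somatic antidepressant treatments".

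**The concern.** The rule and the hypothesis do not match. The hypothesis needs a rise, at three named regions, beyond what sham shows. The rule needs only a significant before-after difference somewhere in the FC maps. A significant fall, or a change in a region that nobody named, meets the rule without supporting the hypothesis.

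This matters because the primary aim is to demonstrate target engagement, and this sentence is the only one that says what engagement means for FC. The criterion is stated in the article itself, so it is not a detail left open for a later analysis plan. If the result is a fall, the report could truthfully say that the pre-specified engagement criterion was met while the pre-specified hypothesis failed.

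**Working it through.** The plan gives no error rate or power for this rule, so there is no figure of its own to reproduce. The check compares how often the rule fires as written and with a positive sign added.

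**Inputs**
- Rule: significant paired t-test, no direction (Section 3.12.1).
- Level: 5%, two-sided. Section 3.12.1 does not state sidedness; Section 3.4 refers to two-sided 95% intervals and p ≤ 0.05.
- n = 15, the active arm (Section 3.4). That the paired test is run within this arm is an assumption. With the anticipated 15% dropout, 15 × 0.85 = 12.75, about 13.
- True mean change in units of the SD of the change: 0, −0.25, −0.5 and −0.8. The documents give none, so these are assumptions.
- One test, no multiplicity correction.

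**Formula.** The paired statistic follows a noncentral t with n − 1 degrees of freedom and noncentrality δ = d√n. The rule as written fires with probability P(T < −c) + P(T > c), where c is the upper 2.5% point. With a positive sign required, only P(T > c) remains. For n = 15 and d = −0.5, δ = −0.5 × √15 = −1.94.

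| True change (SD) | n | Fires as written | Fires if the sign must be positive |
|---|---|---|---|
| 0 | 15 | 5.0% | 2.5% |
| −0.25 | 15 | 14.7% | 0.2% |
| −0.5 | 15 | 43.8% | under 0.01% |
| −0.8 | 15 | 82.1% | about 0% |
| −0.5 | 13 | 38.2% | about 0.01% |
| −0.8 | 13 | 75.4% | about 0% |

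**No effect.** The 5% splits into 2.5% up and 2.5% down, so half of the false declarations contradict the hypothesis.

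**Cost of the sign.** By symmetry, for a true rise of 0.5 SD the written rule fires 43.8% of the time, of which under 0.01 percentage points is downward. Requiring a positive sign therefore leaves power in the predicted direction unchanged.

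**Does a sham contrast alone cure it?** No. In a two-sided comparison of 15 with 15 and a fall of 0.8 SD relative to sham, δ = −0.8 × √(15/2) = −2.19 on 28 degrees of freedom, and the test is significant 56% of the time. Nor does the sign alone cure the lack of a contrast: an equal rise in both arms would still count as engagement.

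**The case against.** The strongest reply is that label and hypothesis are separate by design. Section 2 sets out engagement as a before-after change and then states directional predictions. On that view a fall would mean that the metric moved and the prediction failed, and testing a directional prediction two-sided is normal practice. Much of this stands: the hypothesis itself is clearly directional and a fall would not confirm it. What remains is that the label carrying the primary aim can be earned by a result opposite to the prediction. The two-sided test can stay; what is missing is the usual second condition, that the estimate lies in the predicted direction.

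The percentages are also fairly challenged. The 44% and 82% are the ordinary power of a two-sided test against a real fall of assumed size. They show what the rule permits and are not a defect rate of this trial.

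Four stronger readings are tempting, and the documents do not support them:

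- A reader might infer that the plan's own rationale makes a fall in FC plausible. The passages on hyperactivity and on decreases with treatment in Section 1.3 concern sgACC activity. The rationale specific to FC, reduced connectivity at baseline, points to an increase. The remark in Section 1.2 that tTIS may "disrupt pathological oscillatory activity focally and reduce neural synchrony in deep brain structures" concerns neuronal oscillations and is only indirect support.
- A reader might infer that the data could never contradict engagement. A non-significant result would, and with no effect a single test gives one 95% of the time.
- A reader might infer that a fall would be used to justify a larger trial. The Discussion links successful engagement to further imaging, modelling and parameter work. The Abstract and Section 3.4 tie planning of the larger trial to feasibility, tolerability, effect-size and variability estimates.
- A reader might extend the rule to BOLD and CBF. Section 3.12.1 gives neither a significance-based definition of engagement.

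**Conclusion.** The concern holds for FC, as a mismatch between decision rule and hypothesis. As written, a significant decrease, or a change outside the named regions, is labelled target engagement. Half of the false declarations per two-sided test are in the wrong direction, and an assumed true fall of 0.5 SD at n = 15 would be declared engagement about 44% of the time, against about 0% with a sign requirement. These figures rest on one uncorrected two-sided 5% paired test in the active arm; the effect sizes are not from the documents. The unsigned rule is a fault whichever direction is likelier.

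For BOLD and CBF the point is different and smaller. The predicted increase in sgACC activity sits beside a rationale that links successful treatment to a decrease, and the article does not reconcile the two.

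**What to change.** In Section 3.12.1, rewrite the FC rule so that engagement requires a significant active-versus-sham difference in change (two-sided 5%) at dlPFC, vmPFC and insula, with a positive estimate: FC rises in the active arm, and by more than in sham. State that a significant decrease will be reported separately as a change opposite to the hypothesis, and that changes elsewhere in the maps are exploratory.

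Separately, for BOLD and CBF, reconcile in Section 2 the predicted increase with the hyperactivity and treatment-related decrease cited in Section 1.3, before unblinding, so that the direction that counts is fixed.

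The cost is a few sentences. The sign requirement costs no power in the predicted direction, and its small downside is that a decrease can no longer be claimed as confirming engagement. The sham contrast is less sensitive than a within-arm test (by symmetry with the working, 56% against 82% for an assumed 0.8 SD), but the stated hypothesis of superiority to sham already requires it.

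### The primary hypothesis is superiority over sham, but the stated MRI tests compare post with pre and no between-arm test is given for any primary MRI metric

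*Protocol article*

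**What the plan says.** Section 2 (Objectives and hypotheses) states that a course of active tTIS "will induce engagement of the sgACC post-treatment, which will be superior to sham". Section 3.12.1 repeats the comparative intent, expecting "an increase in the BOLD activation and CBF in the sgACC voxels in the tTIS arm but not the sham", with a matching expectation for FC between the sgACC and the dlPFC, vmPFC and insula.

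The tests in section 3.12.1 are these:

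- **FC:** "FC-based target engagement will be defined as statistically significant pre- vs. post-treatment changes in these sgACC FC maps", "as computed with mass univariate paired" t-tests. Just before this, the section says that "contrast analysis on the FC will be run using CONN Toolbox v.22a", without naming the contrast.
- **BOLD activity:** "Pre- vs. post-treatment changes in sgACC time series properties, such as BOLD activity, will be assessed using Wilcoxon signed-rank tests or paired" t-tests, voxel by voxel. No rule is given for when this counts as engagement.
- **CBF:** "pCASL scans will be used for perfusion detection using the BASIL toolset to conduct simple CBF quantification in the sgACC voxels". No test is named.
- **Anatomically connected regions:** further pre/post comparisons of signal variance and FC, on the same pattern.

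The text does not say whether the paired tests are run within each arm or on both arms together. A treatment group × time test is assigned to outcomes only in section 3.12.2, for the continuous secondary clinical measures. Section 3.4 bases the sample size on a mixed-model ANOVA and speaks of a difference between active and sham, but does not say which outcome that model serves.

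**The concern.** A paired test asks whether a metric moved between Visit 1 and Visit 10. It cannot say whether tTIS moved it. Anything that shifts the metric in both arms, such as scanner drift, familiarity with a second scan or a placebo response, counts towards engagement under the FC definition, which has no arm term and no direction. The Discussion itself lists placebo effects among the things the sham control is there to exclude.

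The wording about the tTIS arm but not the sham does not close the gap. Combined with paired tests, it means a small p-value in one arm and a larger one in the other. Two arms with identical true change produce that pattern often, because each test has only moderate power at 15 participants.

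Target engagement is the trial's primary objective, and the Discussion makes successful engagement the reason for further tTIS work. A wrong conclusion here would carry into the next trial.

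**Working it through.** **1. The plan's own figure.** Section 3.4 gives 30 participants (15 per group) for 90% power at f = 0.25 with a mixed-model ANOVA. It does not state the number of repeated measures m or the within-person correlation rho. For a group × time interaction, use a noncentral F with lambda = f² × N × m / (1 − rho), df1 = m − 1, df2 = (N − 2)(m − 1) and alpha = 0.05. Then N = 30 gives 90.3% power at m = 4, rho = 0.5, and 91.5% at m = 3, rho = 0.6. The figure of 30 can therefore be reached under some inputs and cannot be called wrong. It is simply not tied to the MRI outcomes.

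**2. Error rates when tTIS adds nothing.** Inputs:

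- 15 per arm (sections 3.3 and 3.4) and a two-sided 5% level (section 3.4).
- A common standardised change dz in both arms, in units of the SD of change. The documents give no value, so 0 to 0.8 is assumed.

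Paired t-test in the active arm: noncentral t with 14 df and noncentrality dz × √15. At dz = 0.5 this is 0.5 × 3.873 = 1.94 and the rejection probability is p = 0.438. The arms are independent, so the chance of active significant and sham not is p(1 − p). At dz = 0.5 this is 0.438 × 0.562 = 0.246, close to the maximum possible value of 0.25. A two-sample test on change scores is unaffected by a common shift.

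| Assumed dz | Paired test, active arm (n = 15) | Active significant, sham not | Between-arm test of change |
|---|---|---|---|
| 0 | 5% | 5% | 5% |
| 0.2 | 11% | 10% | 5% |
| 0.3 | 19% | 16% | 5% |
| 0.5 | 44% | 25% | 5% |
| 0.8 | 82% | 15% | 5% |

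A simulation of 40,000 trials per scenario (dz = 0, 0.3, 0.5 and 0.8) agreed: the active-arm test rejected in 5.0, 19.6, 43.7 and 82.0% of trials, and the between-arm test in 4.8 to 5.0%.

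**3. Power of the test that matches the hypothesis.** MRI is done twice (section 3.10), so m = 2, df1 = 1 and df2 = 28. With f = 0.25 and N = 30, lambda = 0.0625 × 30 × 2 / (1 − rho) = 3.75 / (1 − rho).

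| Assumed rho | lambda | Power at N = 30 | N for 90% power |
|---|---|---|---|
| 0.3 | 5.36 | 61% | 62 |
| 0.5 | 7.50 | 75% | 46 |
| 0.6 | 9.38 | 84% | 36 |
| 0.7 | 12.50 | 93% | 28 |
| 0.8 | 18.75 | 99% | 20 |

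The 15% dropout in section 3.4 leaves 30 × 0.85 = 25.5, about 26. At rho = 0.5, power is then about 69%.

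**The case against.** The best defence is that a comparison with sham is plainly intended. Section 2 says so, section 3.12.1 repeats it by arm, section 3.4 speaks of a difference between active and sham under a mixed model, and the unnamed CONN contrast could be group × time. A journal article may leave model detail to a fuller document.

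The intent stands, and it rules out a stronger reading: a reader might infer that the sham arm plays no part in the primary analysis. The documents do not support that. They support less: the intent is clear, and the stated tests do not carry it out. The deferral argument does not rescue the text either. The article does more than omit a model: it fixes a definition of FC-based engagement and names its test, and that definition follows directly after the CONN sentence. A later plan would have to overrule it. Section 3.4 does not assign its ANOVA to any outcome.

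Other objections also limit the point:

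- Only FC has an explicit engagement definition. BOLD has paired tests without a decision rule, and CBF has no test.
- The rates are per test. Section 3.12.1 plans mass univariate testing, so they are not the probability that the trial declares engagement.
- The size depends wholly on the assumed shared change, and 0.5 SD lies near the worst case for the two-p-value reading.
- Regression to the mean is not a well-founded mechanism here: Table 1 selects on MADRS, not on any MRI metric.
- Section 1.3 describes decreased sgACC activity with antidepressant treatment, so shared clinical improvement could work against the predicted BOLD and CBF increases. The FC definition, having no direction, gains no such protection.

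**Conclusion.** The point holds as a contradiction between the primary hypothesis and the stated tests. It needs correcting before analysis, because the written FC rule can be met when sham changes just as much as tTIS.

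The contradiction rests on the text alone. Its size rests on assumptions: no tTIS effect, the same change in both arms, 15 analysed per arm and dz between 0 and 0.8. Under these, the per-test false-positive rate runs from 5% to 82% for a paired test in the active arm and from 5% to 25% for significance in one arm only, against 5% for a between-arm test. If the shared change is exactly zero, the paired tests do no harm. Nothing in the documents shows that it is.

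A reader might also infer that the arms will be pooled in one paired test, which would be worse. The text does not state pooling, so no conclusion is rested on it. Nor does the point show that 30 participants are too few, since power for the right contrast depends on a correlation the article does not give.

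**What to change.** In section 3.12.1, define engagement for each primary MRI metric (BOLD power, CBF, and sgACC FC with dlPFC, vmPFC and insula) by the between-arm difference in change. Either a group × time contrast or the Visit 10 value adjusted for the Visit 1 value and the stratification factor sex would serve. Name the CONN contrast accordingly, state the test for CBF, and report each difference with a 95% CI. Keep the paired tests as within-arm description only.

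In section 3.4, restate the power for this contrast with two scans, an explicit within-person correlation and the expected dropout.

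The cost is rewording and modest analysis work on scans already planned. The real price is that a between-arm test is less likely to reach significance than a paired one, and the stated 90% may not survive: it holds at an assumed correlation of about 0.7 or more before dropout, but not at 0.5. A control-region analysis is not part of this repair. Section 3.7 says some off-target areas receive stronger fields than the target, so a nearby region such as the dorsal anterior cingulate would not be a clean negative control.
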